### Treatment modification

Study sessions will be discontinued, should adverse-effects such as acute hypotensive episode (defined by sudden change in blood pressure – drop of 20 mm Hg or SBP < 100) or chest pain, uneasiness, or cramps manifest. Although these are anticipated to be at low event occurrence rate, the event will be medically recorded and dealt with usual clinical practice. During the session, if a patient complains about temperature being too high or too low, then the dialysate temperature will be adjusted to his/her routine prescription and subject will be removed from the study. A report of all such adverse events will be provided to the ethics board.

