### Patient recruitment

The warm dialysate may result in IDH episodes; hence, only stable HD subjects with no prior history of IDH will be recruited for the proposed study. The dialysis nurses will provide the list of all stable patients in the past one month. The principal investigator will review the database of these stable patients. The patients with history of angina, heart-attack, or chronic obstructive pulmonary diseases (COPD) will not be recruited for the trial. Though stable on HD, these patients may be unstable during warm dialysis session. The residual renal function of study subjects should be negligible (defined by urine output of less than 200 mL/day). Only those subjects, who follow 3 times per week dialysis schedule, will be recruited. Subjects satisfying our mentioned criteria will be contacted. The study administrator will explain about the intervention and the potential benefits as well as harms. Agreed subjects will sign the patient information sheet and consent form. A copy of the consent form will be provided to the subject. Total 20 subjects will be recruited for the study.

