### Study interventions and randomization

All recruited subjects will undergo two study sessions: (i) cool dialysis with dialysate temperature at 35.5°C and (ii) warm dialysis with dialysate temperature at 37°C. The dialysis duration for all sessions will be 240 min. In total, 40 study sessions will be conducted. The maximum and minimum interval between two sessions respectively is one month and one week. Minimum of one week gap is maintained to avoid any carry over effect from the previous study session. All dialysis sessions will be performed using high flux (single-use) dialyzer and the Fresenius 4008S machine. Except dialysate temperature, the dialysis prescription and patient medications (phosphate binder, medicine for hypertension, erythropoietin, etc.) will remain unchanged. Patients will also be advised to keep their dietary intake fairly constant during the study period.

Patients are generally fluid overloaded on the beginning of the week i.e. Monday/Tuesday and target ultrafiltration (UF) will generally be set higher on those days. This higher fluid removal requirement may sometimes result in cramps or hypotensive episodes. Warm dialysate may aggravate this situation by vasodilation; hence, no study session will be performed on Monday/Tuesday. The study sessions for a particular patient will be performed on the same day of the week. All the study sessions will be conducted in randomized order, but patient’s existing dialysis schedule will not be disturbed for the purpose of the study.

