#### Secondary outcome measure

Dialysate temperature can potentially change the hemodynamic response. For each study session, patient blood pressure (BP) and heart rate (HR) will be recorded at every 5 minutes during the whole study session. If any sudden change in BP or HR is noticed, the dialysis nurses will be informed and appropriate clinical action will be taken. If hemodynamic response is indicative of hypotensive episode, then study session will be suspended. The schematic flow chart of the study is presented in Figure 1.

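### A subject stopped for hypotension or chest pain on cool dialysate is not barred from the later warm session, while a temperature complaint does end participation

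*Protocol article*

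**What the plan says.** Under Study interventions and randomization, "All recruited subjects will undergo two study sessions": one at 35.5°C and one at 37°C, between one week and one month apart, in randomized order.

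Treatment modification sets out what follows from two kinds of event. For an acute hypotensive episode and certain symptoms, the trigger is a "drop of 20 mm Hg or SBP < 100) or chest pain, uneasiness, or cramps manifest", and the consequence is that the session is discontinued, with the event recorded and managed by usual practice. For a complaint about temperature, "then the dialysate temperature will be adjusted to his/her routine prescription and subject will be removed from the study". Secondary outcome measure covers the hypotension case again: "If hemodynamic response is indicative of hypotensive episode, then study session will be suspended".

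Patient recruitment gives the possibility that warm dialysate causes intra-dialytic hypotension (IDH) as the reason why "only stable HD subjects with no prior history of IDH will be recruited for the proposed study". It also keeps out patients with a history of angina or heart attack, on the ground that they may become unstable in the warm session.

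**The concern.** The section that assigns consequences gives the stronger one to the milder event. Discomfort with the temperature ends participation. Hypotension or chest pain ends only that day's session, and nothing visible says what happens to the subject's other session.

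The order that matters is cool first. Cool dialysate is the condition that the article describes as protecting against hypotension, and warm is the one that it expects to provoke it; on the choice of study days it says "Warm dialysate may aggravate this situation by vasodilation". A subject who becomes hypotensive or has chest pain on the protective condition has shown the vulnerability that the entry rules were written to keep away from warm dialysate. What is at stake is the safety of that subject.

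**Working it through.** The plan states no figure on this point, so the check sets the rules side by side.

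**1. Consequence by event (Treatment modification)**

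| Event | Session | Subject |
|---|---|---|
| Complaint of too warm or too cool | Temperature returned to routine prescription | Removed from the study |
| Acute hypotensive episode, chest pain, uneasiness or cramps | Discontinued | No consequence stated |

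**2. The path.** Randomized order allows cool first. An event in that session stops it. The general rule of two sessions per subject then still applies, and the warm session falls due one week to one month later. No sentence in the article interrupts this. The allocation of order is not stated; if it is 1:1 (assumed), 20 / 2 = 10 subjects have cool first.

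**3. Would the entry rules catch it?** The no-IDH condition is worded for recruitment and is not said to be re-applied between sessions. The exclusion for recurring or persistent hypotension would not catch a single episode, because recurrent means at least half of sessions and persistent refers to pressure between sessions.

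**4. Which stops matter.** Three definitions, with a drop of 20 read as at least 20:

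- Treatment modification: a drop of 20 mmHg, or SBP below 100; no symptoms needed.
- Exclusion criteria: SBP below 90, or a drop of at least 20 mmHg with symptoms.
- Background (IDH): SBP below 90, or a drop of more than 20 mmHg with symptoms.

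Any SBP below 90 is also below 100, and any symptomatic drop of 20 or more is a drop of 20. Every event under the last two definitions therefore triggers the stop. The reverse fails. A symptom-free fall from 150 to 128 (150 - 128 = 22 mmHg), or a fall from 105 to 98 (7 mmHg, SBP below 100), stops the session but is not hypotension under the other two. So only some of the stopped subjects have had IDH in the article's own sense.

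**5. Cost of a bar in pairs.** A full collection is 240 min × 500 mL/min = 120 L before ultrafiltrate. A stop at, for example, 120 min leaves 120 × 500 mL = 60 L, or 50%. That subject's pair, 1 of 20 (5%), is then incomplete whether or not a second session follows. Further complete pairs lost through the bar: 0.

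**The case against.** This is a condensed article. Withdrawal after an adverse event is often set out in the full protocol, and the flow chart in Figure 1 is not shown. No sentence directs staff to give the warm session after a hypotensive stop. Clinicians keep their discretion through usual practice, and the ethics board is told of such events. The opening of Treatment modification speaks of sessions in the plural, which could loosely be read as ending all of them. The article also expects few such events: "Although these are anticipated to be at low event occurrence rate".

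Part of this stands. A bar may exist elsewhere, and discretion would often prevent the warm session. But discretion is not a rule, and Secondary outcome measure refers to the session in the singular. Above all, the section does not merely leave withdrawal unmentioned: it states removal for one event and only session discontinuation for the other.

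A reader might infer more than the text supports:

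- *That every stopped subject ceases to meet the no-IDH condition.* Step 4 shows that this is true only if the event met the IDH definition.
- *That the three definitions make the stopping rule unsafe.* The stopping limits contain the other two definitions and err towards safety. A trigger more cautious than the diagnosis can be deliberate. Using one term for both, and writing suspended in one place and discontinued in another, are drafting matters.
- *That patients prone to hypotension are screened only by the recurring-hypotension exclusion.* Patient recruitment is stricter: no prior IDH, a nurses' list of patients stable over the past month, and "The principal investigator will review the database of these stable patients".
- *That many sessions will be stopped or precision will suffer.* The article gives no basis for a stop rate, and the case for a bar does not depend on one.

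**Conclusion.** The point holds in a limited form. As the article is written, a subject who has chest pain, SBP below 90 mmHg or a symptomatic fall of at least 20 mmHg in the cool session may still receive the warm session, against the stated reason for restricting entry. It should be corrected, since the consequence is a safety risk to an identifiable subject and the remedy is small.

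The number affected cannot be derived from the document and none is claimed; only those with cool first are exposed to this path. Confidence is medium, because the conclusion assumes that neither Figure 1 nor the full protocol contains a withdrawal rule. The difference in definitions is a minor terminology point.

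**What to change.** Add to Treatment modification: 'A subject whose session is discontinued for chest pain, or for hypotension as defined under Exclusion criteria (SBP below 90 mmHg, or a drop of at least 20 mmHg with symptoms), has no further study session, in particular no warm session. Discontinued sessions are reported with the reason, by temperature and order.'

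Leave the wider limits in Treatment modification unchanged as the trigger for stopping a session, and refer to the same trigger in Secondary outcome measure so that the two sections stop sessions on the same event.

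The cost is a few sentences and the ethics board's agreement. No new measurement is needed, since blood pressure is already recorded every 5 minutes. The downside is that such a subject's second session is lost as unpaired data, but the pair was already incomplete.

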### Outcome measure

#### Primary outcome measure

The objective of this clinical study is to investigate the effect of dialysate temperature on removal of both small and large-sized toxins. To quantify the removed toxin mass in an individual study session, the spent dialysate sample will be analyzed for toxin concentration. The removed toxin mass will potentially depend on the pre-dialysis toxin concentration. If pre-dialysis toxin concentration is high then there is a possibility that more toxin mass will be removed; hence removed toxin mass assessed by spent dialysate will be scaled with respect to pre-dialysis serum toxin concentration. This scaled removed toxin mass for both study sessions will be compared using standard statistical *t*-test. The toxin reduction ratio will also be calculated using pre- and post-dialysis toxin concentrations.

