## Methods and design

### Study design and settings

The study is a single center, self-controlled, randomized study involving patients undergoing conventional high-flux dialysis. Patients are not informed about the dialysate temperature *a priori*; however, some subjects may report the warm or cool sensation based on their experience. The study will be conducted at satellite dialysis center of the National University Hospital (NUH), Singapore.

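### The primary t-test is not tied to within-patient differences or to session order, although the trial is a two-session randomised crossover

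*Protocol article*

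**What the plan says.** The protocol article, under Study design and settings, describes the trial so: "The study is a single center, self-controlled, randomized study involving patients undergoing conventional high-flux dialysis". Under Study interventions and randomization, "All recruited subjects will undergo two study sessions", one at each temperature, and "All the study sessions will be conducted in randomized order". Patient recruitment sets the number: "Total 20 subjects will be recruited for the study". On spacing, "The maximum and minimum interval between two sessions respectively is one month and one week", and the lower limit has a stated purpose: "Minimum of one week gap is maintained to avoid any carry over effect from the previous study session". Both sessions of a patient fall on the same weekday, and prescription and medication stay as they are.

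This is a two-period, two-sequence crossover. The article does not say how many patients follow each sequence, or whether the sequences are balanced.

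The only analysis given for the primary outcome is under Primary outcome measure: "This scaled removed toxin mass for both study sessions will be compared using standard statistical" t-test. Neither the pairing of sessions nor the period is mentioned there.

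**The concern.** Two choices are left open, and in a trial of 20 patients both affect the primary result.

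The first is the form of the test. Read literally, the sentence covers a two-sample test that treats the 40 session values as independent. If a patient's two values are positively correlated, that test uses too large a standard error. A real effect of temperature could then be reported as no difference, which is the wrong answer to the question the trial asks.

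The second is session order. The two sessions may be up to a month apart, so some drift between first and second session is possible. A plain paired t-test does not separate drift from temperature. If more patients have warm dialysis second than first, or the reverse, part of the drift is counted as a temperature effect. Sequences can become unequal by chance. They can also become unequal through the rule under Treatment modification that takes patients who complain about the temperature out of the study.

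**Working it through.** **Inputs from the article.** 20 patients, two sessions each; 20 × 2 = 40, which agrees with "In total, 40 study sessions will be conducted". No other figure can be reproduced, because no alpha, power, effect size or standard deviation is given.

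**Assumptions.** Two-sided alpha 0.05. The effect is the one that a paired t-test on 20 patients detects with 80% power. Within-patient correlation ρ and the period effect are not documented, so ranges are shown.

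**Step 1: reference effect.** By the noncentral t distribution with 19 degrees of freedom, 80% power needs a mean difference of 0.66 SD of the within-patient difference.

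**Step 2: two-sample test on the same data.** With session SD σ, the standard errors are

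- paired: σ√(2(1−ρ)/n)
- two-sample: σ√(2/n)

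Their ratio is 1/√(1−ρ). Power and type I error are from 40,000 simulated trials per row.

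| ρ (assumed) | SE ratio | Paired power | Two-sample power | Two-sample type I error |
|---|---|---|---|---|
| 0 | 1.0 | 80% | 82% | 5.0% |
| 0.2 | 1.1 | 80% | 75% | 3.1% |
| 0.3 | 1.2 | 80% | 70% | 2.1% |
| 0.5 | 1.4 | 80% | 55% | 0.7% |
| 0.7 | 1.8 | 80% | 27% | 0.1% |

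The two-sample test is conservative. It does not inflate false positives; it loses sensitivity.

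**Step 3: bias of an unadjusted paired mean.** Let π be the period effect (second session minus first), with n₁ patients in the cool-warm sequence and n₂ in the warm-cool sequence. The mean warm-minus-cool difference has expectation

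temperature effect + π(n₁ − n₂)/n.

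- 10:10: 0/20 = 0, so no bias for any π.
- 12:8: 4/20 = 0.2; with π = 0.5 SD the bias is 0.10 SD.
- 14:6: 8/20 = 0.4; with π = 0.5 SD the bias is 0.20 SD. A period effect of 5% would shift the estimate by 0.4 × 5% = 2%.

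Under simple randomisation, the chance of a 14:6 split or worse in either direction is 2 × P(Bin(20, 0.5) ≤ 6) = 11.5%. Over all randomisations the bias averages to zero.

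**Step 4: variance from an ignored period effect at 10:10.** Here the paired test is unbiased, but π inflates the spread of the differences. From 20,000 simulated trials per case, paired power is 78%, 72% and 50% for π = 0.25, 0.5 and 1 SD. With period adjustment it stays at 80%.

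**Step 5: cost of adjusting.** The adjusted estimate is the unweighted mean of the two sequence means. Its standard error is (s/2)√(1/n₁ + 1/n₂), with 18 degrees of freedom, where s is the pooled SD of the differences:

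- 10:10: 0.5√(0.100 + 0.100) = 0.224 s; power 80%
- 12:8: 0.5√(0.083 + 0.125) = 0.228 s; power 78%
- 14:6: 0.5√(0.071 + 0.167) = 0.244 s; power about 73%

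With no period effect, the unadjusted paired test keeps 80% at all three splits. The cost of adjusting is therefore negligible when the sequences are balanced and modest when they are not.

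**The case against.** The strongest reply is that the article never calls the test unpaired. A paired t-test is also a standard t-test, and it is the natural reading of a self-controlled study in which every patient has both sessions. A full protocol or analysis plan that is not shown may say so. This stands. A reader might infer that the plan ignores the pairing, but the text supports only that it does not specify it.

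A reader might also infer that most of the power is thrown away. That needs both the two-sample reading and a correlation of roughly 0.6 to 0.7 or more. The article gives no correlation. It does hold prescription, medication, weekday, duration and dialysate flow constant within a patient, and it admits both sexes and a wide range of ages. This makes a positive correlation plausible but does not fix its size.

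Thirdly, a reader might infer that period effects bias the result. They do not do so systematically: the order is randomised, the bias is exactly zero at 10:10, and the same-weekday rule and unchanged prescription limit drift. What remains is chance imbalance, imbalance from removals, and added variance. The 14:6 probability assumes simple randomisation, and the article does not state the method.

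Finally, one might argue that the scaled mass is right-skewed and must be logged. Nothing in the article documents its distribution, and a paired analysis depends on the distribution of the differences. A log scale is an option, not the correction of an error.

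These replies limit the point but do not remove it. The article does name a primary test, so this is not mere silence, and the test as named permits an analysis that does not fit the design.

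**Conclusion.** The point holds as an underspecified primary analysis for which a better method is available at little cost; its severity is moderate. If the two-sample reading were followed, power would fall from 80% to about 70%, 55% or 27% at correlations of 0.3, 0.5 or 0.7, with no loss at zero and no excess of false positives. If the test is paired, nothing is lost through pairing, and only session order remains: a chance bias of (n₁ − n₂)/n times the period effect, and at 10:10 a fall from 80% to 72% power for a period effect of 0.5 SD. All power figures assume two-sided 5% and an effect set at 80% paired power; the correlations and period effects are assumed ranges, not figures from the article.

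**What to change.** **Primary outcome measure.** Replace the t-test sentence by one to this effect: scaled removed mass will be compared within patients, adjusted for period, and the warm-minus-cool difference reported with a 95% confidence interval. In practice, take the warm-minus-cool difference for each patient and average the two sequence means with equal weight. For patients with both sessions, a mixed model with temperature and period as fixed effects and patient as a random effect is equivalent.

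**Study interventions and randomization.** State that patients are allocated to the cool-warm and warm-cool sequences 10:10 in blocks. The period term then protects against imbalance caused by later removals.

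**Cost.** Two changes of wording and one degree of freedom (18 instead of 19). If there is no period effect and the sequences end up unequal, power is slightly lower than for the unadjusted paired test: 78% against 80% at 12:8, and about 73% against 80% at 14:6. Analysis on the log scale, giving a warm-to-cool ratio, may be added if preferred.

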#### Secondary outcome measure

Dialysate temperature can potentially change the hemodynamic response. For each study session, patient blood pressure (BP) and heart rate (HR) will be recorded at every 5 minutes during the whole study session. If any sudden change in BP or HR is noticed, the dialysis nurses will be informed and appropriate clinical action will be taken. If hemodynamic response is indicative of hypotensive episode, then study session will be suspended. The schematic flow chart of the study is presented in Figure 1.

**Figure 1 Fig1:**
[figure not shown]
**Schematic flow diagram of the clinical study.**

## Discussion

Cool dialysate is often recommended as a potential maneuver for controlling and/or preventing the incidence of intra-dialytic hypotensive (IDH) episodes. Cool dialysate reduces the body core temperature which leads to vasoconstriction and consequently helps in maintaining hemodynamic stability during dialysis treatment [5]. It is suggested that IDH occurs when cardiovascular response cannot compensate for large volume losses due to excessive UF rate. This can occur under the circumstances when UF rate exceeds the plasma refilling rate and persists for long enough such that reduction in blood volume reaches the critical threshold. Importantly, this critical threshold differs for an individual patient and is influenced by individual cardiovascular response [16]. This emphasizes the need of individualized dialysate temperature for prevention of IDH incidence. Before one aim for individualized dialysate temperature profile, it is important to study the effect of vasoconstriction on toxin removal.

It has been mentioned that blood cooling has adverse effect on solute disequilibrium [12]. In a study of unstable HD patients, cool dialysate (35°C) was associated with significantly greater increase in peripheral vascular resistance [17]. This increased vasoconstriction can potentially reduce the mobilization of toxins from remote compartments to intravascular compartment, thus reducing the dialysis efficacy. Cool dialysate may be good for 4 hour dialysis, but, in the long term, it may culminate into various complications due to less efficient removal of uremic toxins. One such co-morbidity is amyloidosis due to prolonged accumulation of middle molecule marker, β_2_-microglobulin. It will not be wrong to say that cool dialysate focuses only on one aspect of the dialysis treatment i.e. prevention of IDH, but it must be weighed against the plausible unwanted negative influence of impairing an equally important aspect of treatment i.e. uremic toxin removal. Effect of cool dialysate on urea clearance has been studied, and its removal was not significantly affected by cool dialysate [4,7,18,19]. It is because urea is too small in size to experience significant inter-compartmental resistance from cellular membrane and/or capillary endothelium. Also, the rapid equilibration of urea across the cell membrane is essentially due to facilitated transport by selective urea transporters [20]; such transporters do not exist for other similar sized toxins. Hence, it is imperative to study the effect of dialysate temperature on toxin removal other than urea. Interestingly, there is no clinical study which has investigated the effect of dialysate temperature on toxin removal. The proposed clinical trial intends to fill the gap by comparing the toxin removal outcome for cool and warm dialysate. Contrary to cool dialysate induced vasoconstriction, warm dialysate will result in vasodilation and open capillary surface. This will contribute towards enhanced toxin mobilization from remote inaccessible compartments to intravascular compartment and their subsequent removal in the dialyzer. One should also note that warm dialysate may result in incidence of IDH, and so only stable on HD subjects will be recruited for the trial.

Selection of marker toxin is an important aspect in assessing dialysis efficiency. As mentioned earlier, since urea clearance is unaffected by vasoconstriction or by cool dialysate, a better marker should be chosen. In this trial, we are considering both small and large sized uremic toxins, namely, urea, creatinine, phosphate, β_2_-microlgobulin, and uric acid. Last but not least, the method to assess dialysis efficiency is important to compare the two study sessions. Number of criterion like toxin reduction ratio, dialysis adequacy based on Kt/V_urea_, and post-dialytic rebound can be used. The gold standard is to collect the whole dialysate or fraction of it continuously [21], analyze a sample from whole spent dialysate and quantify the removed toxin mass. In this trial, we will collect the whole dialysate in large drums.

Successful completion of this project will encourage clinicians to refrain from one-size-fit-all approach of dialysate temperature. Selby and McIntyre have also recommended the prospect of individualized dialysate temperature [22]. Further research may lead to patient-specific dialysate temperature profiling, which will not only prevent the incidence of intra-dialytic hypotensive episodes but adjusted to also maximize the toxin removal.
